## **2. Scientific justification**

Among critically ill patients who are able to communicate, nearly 60% report pain during their intensive care unit (ICU) stay. Pain experience in the ICU has been demonstrated associated with the occurrence of delirium^3 and post-traumatic stress. Pain's causes are numerous and essentially related to the care management and invasive procedures (catheters, drains removal, post-operative care, patient mobilization during bed bathing and nursing care procedures, wound care, tracheal suctioning...). Pain management relies on a simple strategy that associates: prevention, assessment, pharmacological and nonpharmacological pain treatment. Recent guidelines strongly recommended further effort take pain into account during patients' management in the ICU.

Pain assessment is remains a difficult problem and frequently underestimated in critically ill patients. Use of pain assessment tools is mandatory because it allows adequate control of analgesia by nurse and physician staff. Among the numerous available tools, patient self-reporting is the best indicator of pain level specifically when using pain rating scale (numeric pain scale-NPS or visual analog pain scale-VAS). In the non-communicative critically ill patients, the use of a behavior pain tool is also recommended and the behavioral pain scale (BPS) has been validated in the intensive care unit as reliable and reproductive.

Whereas pain control in intensive care unit relies mainly on pharmacotherapy, several studies have recently shown that regular interruptions in the administration of sedative drugs was associated with a significant reduction in the duration of invasive mechanical ventilation use and a decrease of delirium occurrence, but also in lower length of ICU a stay. In this strategy, pain assessment should be probably reinforced in order to do not expose patients to further pain-related complications. Indeed, other studies have reported higher short-term^12 but also long-term^13 morbidity when patients experience pain in the ICU, namely: patient-

ventilator dyssynchrony, agitation, tachycardia, hypertension, unplanned extubation, and post-traumatic syndrome disorder.

Thus, it is important to propose complementary and alternative therapies for pain management. Non-pharmacological interventions such as music have been evaluated in many studies. A growing body of literature examines the opportunity to deliver a music intervention such as in pediatrics, oncology or neurology and psychiatry. An assessment of the value of music therapy on pain has been the subject of a Cochrane group metaanalysis which concludes to a reduction in pain intensity and analgesic requirements. In critically ill patients undergoing mechanical ventilation, music effects have been evaluated in another Cochrane metaanalysis of studies demonstrating a decrease of anxiety occurrence, heart rate, respiratory rate but also blood pressure.

This approach is particularly interesting since its physiological mechanisms are now better elucidated. Music effects have thus been demonstrated on the different components of pain:

- sensory component by exerting an inhibitory effect on the afferent fibers: activation of the pathways of pain and brain transmission with modulation and control the transmission of the nociception signals at different stages of the nervous system^26
- cognitive component by distracting attention from memories or images : psychic representation of pain in relation to past painful experiences and events associated with painful episodes
- affective component by changing the state of mood and by stimulating the release of endorphins: gives pain a character more or less painful, unpleasant, bearable according to individuals, may even evolve towards states of anxiety or depression

- -behavioral component by acting on hypertonia and psychomotricity: behavior individual in case of pain

Thus, at a time when expert recommendations encourage the development of assessment tools, behaviors and care giving organizations that would improve patient's wellbeing in the ICU, it appears interesting to assess the therapeutic value of music as a nursing intervention in potentially painful nursing procedures in the intensive care unit.

### **3. Objectives and outcomes**

#### **3.1. Primary objective**

To evaluate the length of pain exposure for critically ill patients unable to communicate undergoing mechanical ventilation, whether or not receiving music, during nursing care.

#### **3.2. Secondary objectives**

To evaluate the occurrence of peak pain exposure for critically ill patient unable to communicate undergoing mechanical ventilation, whether or not receiving music, during nursing care.

#### **3.3. Primary outcome**

Total length of pain exposure (minutes) to a BPS score over or equal to 5 divided by total length of nursing procedure

### **3.4. Secondary outcomes**

Total length of exposure to the maximal BPS score (over or equal to 5) among total length of nursing procedure

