| Outcomes                  | Primary: Proportion of pain exposure during nursing procedures.
Total length of pain exposure (minutes) to a BPS score over or equal to 5 divided by total length of nursing procedure
Secondary: Proportion of maximal pain exposure during nursing procedures Total length of exposure to the maximal BPS score (over or equal to 5) among total length of nursing procedure                                                                                                                                                                                                                                                                                                                                                                                                                                                                                                                                                                                                                                                                                                                                                                                                                                                                                                                                          |

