### **4.2 Sample size**

This is a pilot study, whose purpose is to obtain preliminary data and for which it is not possible to calculate a study sample size. The number of patients to be included was fixed at 60, ie 30 patients in each group (morning bed bathing and wound care with and without music).

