#### **6. Data collection**

Demographic and clinical data will be collected prospectively at the bedside on a standardized form. Demographics data: age, gender, reason for ICU admission (medical, emergency surgery, scheduled surgery), comorbidities, reason for mechanical ventilation, ICU length of stay before inclusion. Patients characteristics at inclusion: presence of tracheotomy, chest tubes, central venous catheter, arterial line, gastric tube, surgical drain tube. Nursing care characteristics will be assessed in both groups at baseline; during; and 30, 60, and 120 minutes after the end of the evaluated nursing care. Total length of nursing procedure will be recorded. Data related to pain assessment: Total length of pain exposure (minutes) to a BPS score over or equal to 5; and total length of exposure to the maximal BPS score (over or equal to 5).

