## **8. Statistics**

Quantitative parameters will be described as median (interquartile range [IQR]) and qualitative parameters as number (%). Categorical variables will be compared using Fisher's exact test and continuous variables using the t test or Mann Whitney or Wilcoxon tests depending to sampling distribution. All tests will be two-tailed at the 0.05 significance level with a two-sided hypothesis.

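### The secondary outcome ignores how high pain peaks and can get worse when peaks are lowered, so its direction is not a reliable reading of peak pain

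*Protocol*

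**What the plan says.** Section 3.4 gives one secondary outcome: "Total length of exposure to the maximal BPS score (over or equal to 5) among total length of nursing procedure". The summary in section 1 repeats that definition under the label "Proportion of maximal pain exposure during nursing procedures". Section 6 lists the matching data item, "total length of exposure to the maximal BPS score (over or equal to 5"), next to the minutes at BPS 5 or more. It does not list the maximal level itself.

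The objective that this outcome serves, in section 3.2 and the summary, is "To evaluate the occurrence of peak pain exposure for critically ill patient unable to communicate undergoing mechanical ventilation", with or without music, during nursing care.

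The primary outcome in section 3.3 uses a fixed level instead: "Total length of pain exposure (minutes) to a BPS score over or equal to 5 divided by total length of nursing procedure".

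On size and testing, section 4.2 says "The number of patients to be included was fixed at 60, ie 30 patients in each group", without a calculation, and section 8 says "All tests will be two-tailed at the 0.05 significance level with a two-sided hypothesis". Section 8 allows a t test or a rank test for continuous variables.

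**The concern.** An outcome meant to describe peak pain should improve, or at least not worsen, when the peak comes down. Here the level being timed moves with the patient. If a short severe peak is removed, the next level down becomes the maximum, and that level may have been held for much longer. The numerator can then grow although no minute became more painful. The same arithmetic run backwards lets a new, brief, severe spike look like an improvement.

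This is the only secondary outcome and the only one aimed at peak pain, in a pilot whose purpose is preliminary data. A signal with the wrong sign could misdirect the choice of endpoint for a later trial. The primary outcome would not necessarily warn the reader, because it can stay the same while the secondary outcome moves.

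**Working it through.** The protocol derives no figure for this outcome, so there is none to reproduce. The check applies the definition as written.

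**Which maximum is meant.** The protocol does not say that the maximum is the patient's own. If it were a fixed top score, the bracket requiring 5 or more would be redundant. If it meant any score of 5 or more, the outcome would duplicate the primary. The bracket makes sense only if the maximum varies between patients.

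**Notation, per patient.** T is the minutes of the procedure, D(k) the minutes at BPS level k, and m the highest level reached.

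- Primary (section 3.3): P = [sum of D(k) over k ≥ 5] / T.
- Secondary (section 3.4): S = D(m) / T if m ≥ 5, otherwise 0.

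The height m decides only which minutes are counted. It does not enter the value of S.

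**Effect of lowering peaks.** Suppose all scores above a level c are brought down to c, with 5 ≤ c < m. Then S becomes [sum of D(k) over k ≥ c] / T, which is at least D(m) / T, and P does not change. S rises whenever any time was spent at levels from c to m − 1.

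**Example 1** (20-minute bath, levels assumed): 10 minutes below 5, 9 minutes at 8, 1 minute at 11.

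- As observed: S = 1/20 = 5%; P = (9 + 1)/20 = 50%.
- With the one minute at 11 lowered to 8: S = (9 + 1)/20 = 50%; P = 50%.

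**Example 2** (20-minute bath, levels assumed): 10 minutes at 4, 6 at 5, 2 at 7, 2 at 8. Scores are not allowed below 3, the assumed floor of the scale.

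| Change | Peak | P | S |
|---|---|---|---|
| None | 8 | 10/20 = 50% | 2/20 = 10% |
| Capped at 7 | 7 | 50% | (2 + 2)/20 = 20% |
| Capped at 6 | 6 | 50% | (2 + 2)/20 = 20% |
| Capped at 5 | 5 | 50% | (6 + 2 + 2)/20 = 50% |
| Capped at 4 | 4 | 0% | 0% |
| All scores down 1 | 7 | 4/20 = 20% | 2/20 = 10% |
| All scores down 2 | 6 | 4/20 = 20% | 2/20 = 10% |
| All scores down 3 | 5 | 2/20 = 10% | 2/20 = 10% |
| All scores down 4 | 4 | 0% | 0% |

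Lowering only the peaks multiplies S by 2 to 5. Lowering everything by 1 to 3 points leaves S at 10% although the peak falls from 8 to 7, 6 or 5. S improves only when the peak drops below 5.

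**At the planned size.** Simulation of 30 versus 30 patients, 600 replicates, Mann-Whitney, two-sided 0.05. The score paths are assumed, not taken from the protocol: 20 one-minute scores limited to 3–12, patient means around 4.5 with SD 1, autocorrelation 0.7, about 50% of time at 5 or more.

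| Effect of music | Mean S, control vs music | Significantly worse | Significantly better |
|---|---|---|---|
| None | 11% vs 11% | 2.0% | 3.2% |
| Peaks capped at 6 | 11% vs 30% | 94.5% | 0% |
| Peaks capped at 5 | 11% vs 50% | 100% | 0% |
| All scores down 1 | 11% vs 9% | 0% | 21% |
| All scores down 2 | 11% vs 5% | 0% | 93% |

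Every row but the first describes music that reduces pain. The sign of the result depends on the shape of the reduction.

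**Against the objective.** Section 3.2 asks about the occurrence of peak pain. S reports neither whether a peak of a given height occurred nor how high it was.

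**The case against.** The strongest reply is that the reversal needs a particular shape of effect. It arises when a lowered peak stays at 5 or above and joins time already spent at the lower levels. A hard cap is the most extreme case, since it supposes that music has no effect at all on the primary outcome. Under uniform shifts the outcome holds or improves. Under a milder compression (the part of the score above 3 reduced by a quarter), results on other assumed paths ranged from almost no change (11.7% to 11.8%) to a modest rise (10.7% to 13.0%). All of this stands. A reader might infer that the outcome always worsens when peaks are blunted, or that a significant result must have the wrong sign. The documents support neither: the definition makes the reversal possible, not certain.

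A second reply is that a share of time is one way to express exposure, so the outcome is not unrelated to the objective. That is fair; the match is poor rather than absent.

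A third is that this is a secondary outcome in a pilot, and that no sample size or decision rule depends on it. That also stands, and it limits the weight of the point. It does not remove it, because the protocol itself fixes the definition in three places. This is not a detail left to a statistical analysis plan.

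**Conclusion.** The point holds in a limited form. With the patient's own maximum as reference, the outcome is blind to the height of the peak and can worsen when pain strictly falls: from 5% to 50% in the first example, with the primary outcome at 50% throughout. That arithmetic, and the direction under capping, follow from the definition. How often and how strongly a reversal would appear depends on the real score paths and on how music acts, and the protocol gives neither. The simulated percentages are therefore illustrations, not forecasts.

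The conclusion rests on reading the maximum as patient-specific, which is the natural reading but is not written out. It would be going too far to say that no result on this outcome could be interpreted, or that the primary comparison is compromised: the primary uses a fixed threshold and does not share the defect. The outcome should be changed, but it does not put the trial's main comparison at risk.

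**What to change.** In section 3.4, the summary and section 6, replace the outcome with the maximal BPS level reached between the start and the end of the procedure. Put peaks below 5 in one lowest category. Compare the groups on it as an ordinal value, by Mann-Whitney, with an effect estimate and its 95% confidence interval. This measure cannot rise when a peak falls, and it fits the objective better. The proportion of patients whose peak reaches a prespecified level may be added, which addresses occurrence directly.

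The lowest category is needed because section 5.4 ties scoring during the bath to variations involving a score of 5 or more, so scores below 5 during the bath are not planned to be recorded. For the same reason a time-averaged BPS over the bath is not a usable substitute: it would need a new assessment schedule.

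The cost is a wording change in three places and one added field for the maximal level. The nurse must already identify that level in order to time exposure to it, so the extra work is small.

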## **4. Conception of the study**

### **4.1 Study design**

A prospective, interventional, comparative, single center study.

### **4.2 Sample size**

This is a pilot study, whose purpose is to obtain preliminary data and for which it is not possible to calculate a study sample size. The number of patients to be included was fixed at 60, ie 30 patients in each group (morning bed bathing and wound care with and without music).

### **4.3 Eligibility criteria**

#### **4.3.1 Inclusion criteria**

- adults patients admitted in intensive care unit if they were older than 18 years of age
- receiving invasive mechanical ventilation,
- with a Richmond Agitation Sedative Scale (RASS) score between -3 and +4.

#### **4.3.2 Exclusion criteria**

-adults patients receiving neuromuscular blocking agents

-adults patients with a RASS score <-3

### **5. Intervention**

#### **5.1 Modalities of enrolment**

In this study, eligible patients will be consecutively included. The first 30 patients will be included in the control group and the next 30 patients in the intervention group.

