| Intervention              | Eligible patients will be consecutively included. The first 30 patients will be included in the control group and the next 30 patients in the intervention group. In the intervention group, patients will be exposed to music during the morning bed bath, using headphones connected to an MP3 converter via a Bluetooth connection. The same selection of passages by Mozart will be used in all patients. The music will start at the same time as the bed bath and continued throughout the bath and for 30 minutes after the end of the bath. Sound intensity will do not exceed 60 decibels. In both groups, BPS scores will be determined by a nurse, who will not be involved in providing the bath. The BPS score will be determined just before the bath; at completion of the bath; and 30, 60, and 120minutes after the end of the bath. During the bath, the BPS score will be assessed in cases of variations of BPS score $\geq 5$ . Total length of the bath will be recorded.                                                                                                                                                                                                                                                                                                                                             |

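### Allocation by order of entry (first 30 control, next 30 music) fully confounds group with calendar period, so a music effect cannot be told apart from a period effect

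*Protocol*

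**What the plan says.** Section 5.1 of the protocol gives the order of inclusion, "In this study, eligible patients will be consecutively included", and then the allocation rule, "The first 30 patients will be included in the control group and the next 30 patients in the intervention group". The Intervention row of the summary (section 1) states the same rule, so the two places agree.

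Section 4.1 describes the design as "A prospective, interventional, comparative, single center study". It uses neither the word randomised nor before-after. Section 4.2 sets the size: "The number of patients to be included was fixed at 60, ie 30 patients in each group". It presents the study as a pilot "for which it is not possible to calculate a study sample size".

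Section 8 compares the groups on "continuous variables using the t test or Mann Whitney or Wilcoxon tests depending to sampling distribution", and adds "All tests will be two-tailed at the 0.05 significance level with a two-sided hypothesis". The title names the analgesic effect of music as what is being evaluated, and both outcomes in sections 3.3 and 3.4 are pain outcomes.

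**The concern.** Inclusion is consecutive, so order of entry is calendar order. Patients 1 to 30 form one period and patients 31 to 60 the next, with no overlap. The control group shows what pain looked like in the earlier period, not what it would have been without music in the later one.

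The protocol itself leaves several features free to differ between the two periods:

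- Analgesia and sedation are titrated as needed (section 5.4).
- Surgical dressings may be evaluated as well as bed baths (section 5.2), so the mix of procedures can change.
- Eligibility covers a wide RASS range (section 4.3.1), and medical, emergency surgical and scheduled surgical admissions are all recorded (section 6), so case mix can change.
- The outcome is rated by nurses, and scoring during the bath depends on someone noticing a change (section 5.4), so scoring habits can change.

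Allocation is also fully predictable. Whoever screens a patient or approaches a relative for consent knows which group comes next.

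At stake is the one comparison the study exists to make. If the result is to inform a later trial, the effect estimate carried forward would be music plus period, in unknown proportions.

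**Working it through.** **Inputs.** From the protocol: 30 patients per group and 60 in total (section 4.2), two-sided alpha of 0.05 (section 8), allocation by order of entry (section 5.1). The total is consistent: 30 + 30 = 60. There is no power-based figure to reproduce, because the protocol gives no effect size, SD or power. It also gives no period effect, so every drift below is an assumption, expressed in SD units of the outcome.

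**Step 1: can group and period both be estimated?** Code group as 0 for patients 1–30 and 1 for patients 31–60. A period indicator has exactly the same values. A model with intercept, group and period has three columns but rank 2, so a step change between periods cannot be separated from music.

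**Step 2: can a smooth trend be adjusted for?** The correlation of group with order of entry is the covariance divided by the two SDs.
- Covariance: 0.25 × 30 = 7.5, because the groups' mean positions are 30 places apart.
- SD of group: 0.5.
- SD of order: √((60² − 1)/12) = 17.32.
- r = 7.5 / (0.5 × 17.32) = 0.87.
- Variance inflation: 1 / (1 − r²) = 4.0.

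Adjustment for a linear trend is therefore possible only if the trend is assumed to be linear, and it multiplies the variance of the group effect by about four.

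**Step 3: false-positive rate under an assumed step difference, with no music effect.** The t statistic follows a non-central t with 58 degrees of freedom and non-centrality d × √(30/2) = d × 3.873, where d is the period difference in SD.

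| Assumed d | Non-centrality | Rejection at nominal 5% |
|---|---|---|
| 0.10 | 0.387 | 6.7% |
| 0.25 | 0.968 | 15.9% |
| 0.50 | 1.936 | 47.8% |

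**Step 4: gradual drift, and the same drift under randomisation.** If the outcome drifts linearly by D from the first to the sixtieth patient, the group difference is D × 30/59, about half of D. The rates below are simulated with normal outcomes and no music effect (10,000 runs for sequential allocation, 4,000 for permuted blocks of 4).

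| Assumed D | Group difference | Sequential, t test | Sequential, Mann-Whitney | Randomised blocks, t test |
|---|---|---|---|---|
| 0.25 SD | 0.13 SD | 7.8% | 7.1% | 4.7% |
| 0.50 SD | 0.25 SD | 16.0% | 14.8% | 4.5% |
| 1.00 SD | 0.51 SD | 47.4% | 44.9% | 3.9% |

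The rank test gives little protection. Concurrent allocation of the same 60 patients keeps the rate at or just below 5%.

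**The case against.** The strongest reply is that this is a disclosed design for a declared pilot. The sequential rule is stated openly and identically in both places, and the protocol never claims randomisation. It also contains real safeguards: consecutive inclusion limits discretionary selection, the bath is described as standardised, sedation follows one unit protocol, and the scoring nurse does not give the bath. Pre-bath BPS and admission characteristics are collected, so measured imbalance can be examined. Covariate adjustment may be set out in an analysis plan that is not shown. Sequential blocks also avoid carry-over through nurses who would otherwise care for both groups.

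Much of this stands. The point is a design weakness, not a contradiction, and the short list of tests in section 8 is not a second defect. The safeguards make a large drift less likely, and carry-over through staff is a fair argument, although the protocol does not make it. None of this supplies a concurrent control, however. Covariates correct only for what was measured, and no analysis plan can separate two indicators that are identical. The pilot label softens the consequence but does not remove it, since the study still tests pain outcomes between groups at 0.05 and states no feasibility objective.

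A reader might infer that the result will be biased, or biased in favour of music because starting a pain study sharpens bedside pain care. The documents support neither. They show that a period effect could not be distinguished, not that one exists. Control patients are scored within the study too, so the direction is unknown.

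**Conclusion.** The point holds as a risk built into the allocation rule. The effect of music is identifiable only under the assumption that nothing else relevant differed between the two periods, and the data cannot test that assumption. Predictable allocation adds a possible difference in who is screened and consented, which consecutive inclusion limits but does not exclude.

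The size depends wholly on the drift. For between-period differences of 0.10, 0.25 and 0.50 SD, the nominal 5% test rejects about 7%, 16% and 48% of the time when music has no effect. Reaching those differences through gradual linear drift needs about twice as much total drift over the study. These rates are illustrations and should not be read as the expected error rate of this study.

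**What to change.** In section 5.1 and the Intervention row of the summary, replace allocation by order of entry with 1:1 concealed randomisation of the same 60 patients, in permuted blocks of varying size, by sealed opaque envelopes or a web list. Reveal the group only after consent and after the pre-bath BPS, which section 5.4 already requires. State the randomised design in section 4.1.

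The cost is a protocol and ethics amendment, preparing and keeping the allocation list, and staff switching between music and no music throughout instead of changing once. Carry-over through staff becomes possible, because the same nurses may care for both groups. The sample size need not change.

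If recruitment can no longer be changed, describe the design in section 4.1 as a non-randomised sequential (before-after) comparison and limit the conclusion to a preliminary association. That costs only wording, but it leaves the confounding in place.
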